## RESEARCH PROTOCOL

More than 400,000 Americans die each year from a smoking-related illness. Of the more than 43 million smokers in the United States today, 1 in 2, or more than 20 million, will die prematurely due to their smoking habit. Approximately 1/3 of these patients will die from smoking-related complications of chronic obstructive disease (COPD).

More than 15 million Americans currently suffer from COPD. Mirroring the distribution of cigarette smoking, COPD disproportionately affects the poor and disadvantaged. COPD can have a profound impact on quality of life, resulting in difficulty breathing, chronic cough, poor exercise tolerance, disability, hospitalizations, and death. Smoking is the primary cause of COPD, and quitting smoking is at the cornerstone of COPD treatment. For patients with COPD, quitting smoking can reduce the risk of further lung deterioration as well as the risk of COPD-related hospitalizations, death, and disability.

Although smoking cessation is strongly recommended for all patients with COPD, patients with COPD have a particularly high dependence on nicotine and find it extremely difficult to quit. Despite the ongoing damage to their lungs, more than 39% of people suffering from COPD continue to smoke. It's not that these smokers don't recognize the danger of their habit – they do. The vast majority would like to quit, and each year half try, but only about 3% actually succeed in quitting.

The current standard of care for smoking cessation in the United States asks smokers to quit completely on a selected quit date, ideally with the aid of a smoking cessation treatment such as varenicline, bupropion, or nicotine replacement therapy (NRT). This approach is unrealistic and unsuccessful for the majority of smokers; they find the idea of quitting cold turkey daunting and don't even try. At any given time only 10-20% of smokers are ready and willing to make a quit attempt. Even for the motivated smokers who are willing to quit right away, 80% fail in the attempt and quickly resume smoking. Not surprisingly, many smokers would like to have alternatives to this 'cold turkey' approach; they are interested in gradual tapering or cutting down on the number of cigarettes that they smoke until they are ultimately able to quit.

In this study, we seek to compare the current standard of care (smoking cessation) with long-term guided maintenance therapy on NRT. In this randomized controlled trial, smokers with COPD will be randomized to receive either: 1) a standard smoking cessation (SSC) intervention consisting of counseling and NRT for smokers ready to quit; or 2) long-term guided maintenance therapy (LT-NRT) in which all smokers, regardless of their immediate interest in quitting, are treated with NRT and encouraged to cut down on their smoking and quit more gradually. Evidence suggests that the LT-NRT approach will not only result in lower exposure to toxic cigarette smoke, but will also outperform SSC in terms of smoking cessation by a factor of 2:1. If this holds true for patients with COPD, LT-NRT could dramatically expand treatment options for smokers with COPD and make treatment much more approachable to the millions of patients with COPD who continue to smoke but are intimidated by the idea of immediately quitting.

In addition to directly comparing the benefits of SSC versus LT-NRT, our study will perform a classification and regression tree (CART) analysis that will result in the development of a clinical decision tree. This decision tree will provide smokers with estimates of their chances of quitting or significantly reducing their smoking based on their treatment choice and their own personal characteristics. This decision tree will facilitate the dissemination of the findings of this study as it can be posted on the web or incorporated into the patient's electronic health record. This decision tree will help smokers and their clinicians choose a treatment that matches their individual characteristics and their own desired outcomes. Our study could also inform reimbursement policies related to smoking cessation and NRT by providing evidence of the utility of long-term NRT maintenance therapy.

*Why focus on smokers with COPD?* Although we could have conducted this study within any population of smokers, we chose to focus on smokers with COPD because they are particularly vulnerable to the adverse effects of smoking. A study in patients with COPD is more likely to demonstrate differences in clinical outcomes that could capture the attention of policy makers. Moreover, clinicians and stakeholders may be

more willing to adopt the LT-NRT intervention in COPD patients since the benefits of cutting back or quitting appear particularly salient in this group. (This supposition was confirmed by our stakeholders.) Nevertheless, our findings could have important implications for the entire population of smokers and could help advance treatment for the 43 million smokers in the United States.

In addressing cigarette smoking and COPD, we are actually addressing multiple chronic diseases at once. Cigarette smoking itself has been characterized as a chronic disease and cigarette smoking is directly related to heart disease, chronic lung disease, and multiple types of cancer. Smoking increases the risk of developing diabetes and osteoporosis. It increases the risk of periodontal disease, peptic ulcer disease, impotence, and reproductive disorders. Given the relationship of smoking to so many chronic conditions, smoking cessation has been identified as one of the most important and cost-effective preventive health interventions available.

## **Explain how the results of the study would likely improve health care and outcomes (*Criterion 2*)**

In this section, we will show how our proposed study is strongly grounded in research on the potential benefits of using combination NRT, using extended treatment for smoking cessation, and providing NRT treatment prior to actually quitting. We will show, however, that this research, for a variety of reasons has not yet been translated into clinical practice, reimbursement policies, or informed treatment choices for patients. We will show how our research is highly responsive to research priorities outlined by expert groups and well aligned with the needs and interests of patients. Perhaps most importantly, we will show how the findings of our research could be quickly disseminated and have a profound impact on the current treatment of smokers with COPD and improve outcomes for this high-risk population.

### ***Benefits of combined NRT therapy***

We selected combination NRT as our pharmacological treatment for this study because NRT is the smoking cessation treatment most commonly used by smokers and was strongly supported by our Patient Advisory Panel. NRT has fewer side effects than either bupropion (Zyban) or varenicline (Chantix), and combination NRT appears to be at least as effective as any of the other pharmacological treatment for smoking cessation. Combination therapy with NRT involves combining a long-acting nicotine product (i.e. nicotine patch) with a short-acting nicotine product (e.g. nicotine gum or nicotine lozenge); combination therapy has been found to be more effective than using either agent alone (RR 1.34, 95% CI 1.18 to 1.51). Combination therapy with NRT results in quit rates comparable to those seen with varenicline (Chantix) without some of the concerns related to side-effects. When NRT is used as monotherapy (e.g. gum or patch alone), smokers typically receive a lot less nicotine than they get by smoking. Not surprisingly, therefore, some highly dependent smokers appear to exhibit a 'dose-response relationship' with NRT with those receiving higher doses having higher quit rates. By using combination therapy, participants in this study should receive dosing of therapeutic nicotine closer to what they procure through their smoking. The patch will provide a steady dose of nicotine that reduces withdrawal and craving while the gum or lozenge will allow the smoker to personally titrate the dose of nicotine to the dose that is most effective. Although clinical practice guidelines recommend NRT combination therapy as a first-line treatment for smoking cessation, most insurers do not cover it, and it has not been widely implemented in clinical practice. Positive results from our study would provide strong support for changing the standard of care related to use of combination NRT in high risk patients.

### ***Benefits of extended treatment***

Current practice guidelines recommend providing NRT treatment for 6-14 weeks. For smokers willing to make an immediate quit attempt, use of extended treatment has led to mixed results, leading to recommendations by expert groups for more research on the benefits of extended therapy. Medication adherence has been an issue with many studies on extended pharmacotherapy and could account for some of these mixed results. On the other hand, in studies of continuing smokers not willing to quit immediately, the use of extended NRT has led to a 2-fold increase in cessation compared to short term treatment. Meanwhile, 8-10 weeks of NRT remains the treatment standard and insurance programs such as Kansas Medicaid place tight limits on the duration on treatment. Extended treatment with NRT has not been studied in

patients with COPD. The findings from our study, therefore could have a profound impact on guideline recommendations and reimbursement policy related to duration of therapy with NRT in smokers with COPD.

### **Importance of adherence**

Discussions on duration of use may be moot if adherence is not addressed. Pharmacotherapy adherence has been consistently linked to improved treatment outcomes, and adherence to the prescribed dose and treatment length is necessary to achieve maximum drug effect. Low adherence rates may lead to underestimates of the potential effectiveness of NRT. When smokers who are trying to quit ‘slip’ and have a cigarette, they may feel that the NRT is not working and quit taking it. In reality, ‘slips’ while on NRT may be a sign that they should be raising the dose (e.g. using more nicotine gum). Our counseling in both arms of this study will specifically address ‘adherence support’ thereby increasing the validity of our study findings.

### **Efficacy and safety of precessation treatment**

Use of NRT while the patient is still smoking has a strong grounding in addiction theory. If nicotine receptors in the brain are already saturated with nicotine derived from patch or gum, then the nicotine obtained from cigarettes won’t be able to provoke a strong ‘reward’ stimulus in the brain – thereby effectively ‘extinguishing’ the behavioral reinforcement from smoking. This theory is supported by empiric data. Smokers using NRT spontaneously reduce the amount that they smoke – even if they aren’t actively trying to quit. Indeed, it appears that smokers receiving NRT adjust (reduce) the amount that they smoke in order to maintain their usual nicotine intake. The result of this is that smokers who use NRT while still smoking not only reduce their exposure to cigarette smoke, but are also twice as likely to quit smoking.

Use of NRT while the patient is still smoking is safe. While labels on NRT products in the US continue to caution smokers and clinicians about the potential hazards of using NRT while still smoking, there is extensive evidence that the risk of harm is virtually non-existent. Nicotine is a sympathomimetic drug that can increase heart rate, increase blood pressure and contribute to endothelial dysfunction, but the dose-response curve for these effects appears to be relatively flat, so that when someone is already smoking, adding additional nicotine appears to have little effect on the cardiovascular system. In addition, clinical trials of NRT in patients that already have cardiovascular disease have revealed no increased risk with use of NRT compared to placebo. Researchers and policymakers in the United Kingdom recently completed an extensive safety analysis on use of NRT while smoking. They not only concluded that this practice was safe, but also officially approved the use of NRT for continuing smokers trying to reduce smoking prior to quitting. In the United States, however, NRT is still reserved for smokers willing to go ‘cold-turkey’ and quit immediately.

### **Matching patients with optimal treatment based on their own characteristics**

Our classification and regression tree (CART) analysis will allow us to provide more personalized recommendations for smokers with COPD and facilitate dissemination. CART is an analytical approach used as an alternative to logistic regression for the identification of subgroups of individuals who may have differential response to treatment. It can be used to develop a decision tree to guide clinical decision making. CART uses statistical methods to cluster individuals into different groups that have different outcomes related to the treatment. Using CART, multiple individual characteristics (e.g., gender, cigarettes

per day (cpd), cotinine level, readiness to quit, treatment assignment, etc.) can be considered simultaneously and variables can be identified that efficiently separate individuals into groups that are more or less likely to experience a positive outcome (e.g., abstinence). These variables can then be incorporated into a decision tree that will show the predicted outcome (response to treatment) based on a patient's given characteristics. The total number of splits or branches in the resulting decision tree depends on the number of critical variables identified in the CART analysis. The complexity of the decision tree can adapt itself to the complexity of the data. As a nonparametric approach, CART does not require specification of the nature of the relationship between predictors and outcome or a priori assumptions about the true model.

The decision trees developed using a CART analysis have good face validity and can be easily applied clinically – the user simply follows the branches of the decision tree that are relevant to the specific individual. CART models have been developed in many areas of healthcare, including tobacco research. We propose to employ the CART approach to calculate abstinence rates for different subgroups using clinically relevant variables identified by literature review and our patients and stakeholders. The resulting decision tree will allow any smoker with COPD estimates to use their own personal characteristics to estimate their chances of stopping smoking given a specific treatment choice (Aim 2). The probability of other relevant outcomes (e.g. risk of worsening lung function) can be calculated for each branch of the decision tree as well. The ease of use of this type of decision tree will allow ready dissemination via web or smartphone applications or incorporation into clinical decision algorithms within electronic medical records.

Our proposed research is highly responsive to many of the research priorities identified in the *Clinical Practice Guideline for Treating Tobacco Use and Dependence*. These guidelines identified the need for more research related to long-term medication use for smoking cessation and the need for more studies on the use of NRT prior to quitting smoking. The guidelines further identified the need for more studies on treatment of highly dependent smokers, including studies on use of combination medication therapy. The guidelines also identified a need for more research on ways to give smokers greater hope and confidence in treatment opportunities and to make treatment of tobacco use more accessible to smokers (e.g. those not yet ready to quit). Our proposed research addresses each of these research priorities.

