### Analytical Plan.

**Sample Size and Power Calculations.** Our sample size was based on our primary outcome, point-prevalence abstinence at Month 12, using an intent-to-treat approach. Based on prior studies using precessation NRT, we estimate a 2-fold increase in cessation outcomes in the LT-NRT group compared to the SSC group. Given our recruitment of patients at all levels of readiness to quit, we estimate a 12 month cessation rate of 10%. With 199 participants, in each arm, we will have an 80% power to detect a 2-fold difference or greater with a Type I error rate of 5%. This sample size will provide comparable power for looking at 6 month sustained cessation. For the CO measured longitudinally at four time points, we have 80% power to detect a mean difference of 2.24 ppm. Likewise, for NNAL, we have 80% power to detect a mean difference of 0.41 pmol/mg creatinine or more between the two groups.

**Specific Aim 1: Compare the benefits of traditional smoking cessation (SSC) versus long-term guided maintenance therapy (LT-NRT) with NRT.** The chi-square test will be used to compare the verified 7-day point prevalence abstinence at Month 12 between the two groups. If there is imbalance between treatment groups at baseline, we will switch to logistic regression for our primary analysis. We will use similar methods to test for group differences for dichotomous secondary outcomes including sustained abstinence and proportion with 1 or more ED visits or hospitalizations. To test for differences in change in respiratory symptoms and FEV1 from baseline measured at 3, 6, and 12 months, we will use standard mixed models repeated measures analysis. Likewise, to test for differences in longitudinal exposure to CO and NNAL, we will compare the area under the curve over the entire 12 months of follow-up using repeated measures analysis. If the treatment differences are heterogeneous across any covariate sub-groups, we will quantify and report such interactions

with appropriate contrast statements. We will compare the cumulative number of self-reported quit attempts by means of a Wilcoxon rank-sum test.

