**Specific Aim 2: Develop estimates of patient-desired outcomes based on patient-specific characteristics and treatment choice (SSC vs. LT-NRT)** We will employ a Classification and Regression Tree (CART) analysis to identify subgroups of participants whose personal characteristics might impact the benefit of treatment. The resulting decision tree will allow smokers and their care providers to estimate their individual chances of success given their choice of treatment. To maximize the utility of the decision tree, we will start by soliciting input from our Stakeholder Advisory Committee and Patient Advisory Panel. We will ask them to identify key demographic, psychosocial, biological, and smoking factors from Table 5 and help us convert them into clinically meaningful binary variables that could be tested for inclusion in a clinically meaningful decision tree. (Drs [name] and [name] will provide both groups with simple conceptual models to assist them in providing meaningful, independent contributions.) The candidate variables, along with treatment assignment (LT-NRT vs SC) will be entered into a recursive partitioning model as described by Brieman and Friedman using the RPART package in the R statistical software. Specific methods related to building the tree (using appropriate splitting criteria and loss incorporation using the altered priors method), pruning the tree and handling missing data (using surrogate variables) will be deployed using the techniques described by Therneau et al. Given the event rates expected and overall sample size, a validation subsampling scheme will not be feasible, thus we will utilize 10-fold cross-validation on the regression tree to assess its properties. Additionally, we will account for the uncertainty in tree classification by generating a bootstrap sampling distribution of the CART as described by Shalizi. In addition to developing a CART model/decision tree for smoking cessation, separate classification models will be developed for other high priority binary outcomes, including: 1) 6 month sustained abstinence; 2) 50% reduction in carcinogen (NNAL) exposure; and 3) COPD related hospitalization (yes/no). (These were the models of greatest interest for our initial Patient Advisory Panel, but other outcomes could be modeled as well if our patients and stakeholders think that these additional models might be useful.)

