The most prominent guideline related to tobacco control policy is the guideline produced by the US Preventive Services Taskforce. Our investigators know many of the authors of these guidelines personally and interact with them at national meetings, in particular through the Society for Research on Nicotine and Tobacco. We will work with these guideline developers to see if the findings of our study can be incorporated into the next update of these guidelines. Incorporation of study findings into clinical practice guidelines can have tremendous implications for driving policy changes that can drive implementation of these findings.

Dissemination to patients, stakeholders (particularly clinicians), and policymakers, as outlined above, are critical to implementation, but implementation will also be facilitated by the publication of our 'decision tree' which will help patients and clinicians understand the relative merits of treatment choices given the smokers unique characteristics (Aim 2). This decision tree will be published on the web and made accessible world-wide. We propose to incorporate the decision tree into our own EPIC electronic health record at KUMC and share this adaptation to the EPIC learning community. EPIC is the most widely used electronic health record in the United States and EPIC users have a variety of tools available for sharing innovations across institutions, including an EPIC users group associated with the NIH's Clinical and Translational Research Centers program of which KUMC is a member. As the decision tree gains acceptance, it can be distributed across other electronic health record platforms.

Perhaps the most important step in the implementation of study findings will be related to making changes in insurance coverage for NRT. Insurance coverage for NRT varies substantially across health plans, but in general, insurance companies have placed limits on the duration of NRT use and do not cover combination therapy. [name] has been directly involved in working with state Medicaid programs on revising coverage of services for smoking cessation. Given specific provisions within the affordable care act, making these changes in coverage decisions will be much easier if the findings of this study are incorporated into

clinical practice guidelines – as noted above.

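### Aim 2 branch rates will tend to overstate the gap between best and worst branches, and no stated step corrects them before they reach patients

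*Protocol*

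**What the plan says.** The section *Matching patients with optimal treatment based on their own characteristics* makes the branch rate the output of the tree: "We propose to employ the CART approach to calculate abstinence rates for different subgroups using clinically relevant variables". The Analytical Plan, under Specific Aim 2, says how it will be used: "The resulting decision tree will allow smokers and their care providers to estimate their individual chances of success given their choice of treatment".

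The same paragraph describes the method:
- Candidate variables are chosen from Table 5 with the patient and stakeholder panels, made binary, and entered with treatment assignment into RPART.
- Loss is handled through altered priors, the tree is pruned, and surrogates deal with missing values.
- Holding back a validation sample is ruled out because of the event rate and sample size, "thus we will utilize 10-fold cross-validation on the regression tree to assess its properties".
- A bootstrap distribution of the tree is added to reflect uncertainty in the classification.

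On release, the Dissemination and Implementation Potential section says: "This decision tree will be published on the web and made accessible world-wide". It also proposes building the tree into the electronic health record.

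**The concern.** A tree picks splits because they separate the observed rates. If the rates are then read from the same people, the highest branch is partly high by chance and the lowest partly low by chance. Cross-validation can choose a tree size and estimate prediction error, but it does not alter the rate printed in a branch. A bootstrap used to show variability does not alter it either.

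This matters because the rate is the product. It is meant to help a smoker choose a treatment. Someone in the top branch would tend to see too high a chance of quitting, and someone in the bottom branch too low a chance.

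**Working it through.** **1. Events available.** The Analytical Plan says: "With 199 participants, in each arm, we will have an 80% power to detect a 2-fold difference or greater". It assumes 10% abstinence in SSC and "we estimate a 2-fold increase in cessation outcomes in the LT-NRT group compared to the SSC group", so 20% in LT-NRT. Two-sided 5%, pooled variance, no continuity correction:

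n = [1.96·√(2·0.15·0.85) + 0.8416·√(0.10·0.90 + 0.20·0.80)]² / 0.10² = (0.990 + 0.421)² / 0.01 ≈ 199 per arm.

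The stated figure reproduces. Expected quitters: 0.10·199 + 0.20·199 = 19.9 + 39.8 ≈ 60 of 398. These events support the whole tree.

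**2. Simulation of the described procedure (R rpart).** The protocol gives no figure for the tree, so the following are assumptions: 398 patients; treatment plus 10 to 20 binary candidates, each 50% prevalent; Gini splitting; equal priors; 10-fold cross-validation; pruning at the minimum cross-validated error or by the 1-SE rule; 200 runs per setting. The treatment log-odds ratio was 0.81, that is ln[(0.20/0.80)/(0.10/0.90)] = ln 2.25. The 12-candidate runs centre on logit(0.13) = −1.90, so with treatment alone the arms are at logits −1.90 ± 0.405, about 9% and 18%. In each run the displayed gap between the best-looking and worst-looking branch was set against the true gap of those same two branches.

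Results with 12 candidates (mean gaps in percentage points, displayed v true, then ratio):

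| True predictors besides treatment | Minimum-error pruning | 1-SE pruning |
|---|---|---|
| None | 21.1 v 5.9 (3.6) | 13.2 v 6.8 (1.9) |
| Moderate (log-odds 0.6, 0.6, 0.4) | 25.0 v 7.3 (3.4) | 15.8 v 7.7 (2.05) |
| Strong (OR 3, 2, 2) | 29.0 v 13.3 (2.2) | 21.5 v 12.0 (1.8) |
| Very strong (OR 5, 3, 2) | 32.3 v 21.4 (1.5) | 25.4 v 21.2 (1.2) |

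In the moderate setting the best branch showed 29.9% against a true 19.4% (minimum error), or 23.5% against 18.8% (1-SE).

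With 10 and 20 candidates the ratios were 3.1 and 3.7 (treatment only) and 3.3 and 4.0 (moderate) under minimum-error pruning. Under 1-SE pruning they were 1.8 and 1.8, and 2.0 and 2.2. The overall range is about 1.2 to 4.0.

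**3. What pruning and priors do.** Without cross-validated pruning (complexity limit 0.01) the ratio was about 6.5 to 14, so pruning removes a large part of the bias. With observed priors and cross-validated pruning, 95 to 100% of runs had no split and so no gap to overstate.

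**4. Which correction to use.** One obvious remedy is a single calibration slope that pulls every branch toward the pooled rate. Treatment is itself a tree variable, so this also pulls the arms together. Illustration with a slope of 0.31, the mean seen in simulation, and arms at 10% and 20% (pooled 15%): 15 + 0.31·(20 − 15) = 16.55 and 15 + 0.31·(10 − 15) = 13.45, so a 10-point difference becomes 3.1.

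In simulated trees (20 candidates, equal priors, 60 runs per setting; weak or moderate predictors) a displayed contrast of 7 to 8 points became about 3 to 4, against a true value of about 10. The slope was unstable, with SD 0.23 to 0.37. Shrinking toward each arm's own overall rate kept the arm difference. It also gave lower error in individual chances than the uncorrected rates in every setting (RMSE 0.025–0.090 v 0.048–0.112), and lower error than the single-slope version.

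**The case against.** The strongest objection is that this rests on silence. The protocol does not call the rates uncorrected. An analysis plan, not shown here, may deal with optimism, and the protocol points to cited sources for tree building and for the bootstrap. It is true that uncorrected rates are an inference. But this protocol does more than leave the matter open: it sets out the tree method step by step, gives a purpose for cross-validation and for the bootstrap, and offers cross-validation as the substitute for a validation sample. Followed as written, none of the steps changes the rates.

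A reader might also infer that the planned cross-validation does nothing about the bias. That is too strong. If it guides the pruning, it cuts the overstatement substantially (step 3). Some overstatement remained, however, in every equal-priors setting above.

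A reader might further infer that the gap will be overstated severalfold. The documents do not support that as a fact. Three to four fold needs minimum-error pruning and weak to moderate predictors. With 1-SE pruning the ratio is about 2, and with very strong predictors it is 1.2 to 1.5. The protocol fixes neither the pruning rule nor the prior values nor the number of candidates. The observed-priors result also stands, although the plan to use altered priors points away from that setting, and the bias matters whenever a tree with splits is published.

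**Conclusion.** The point holds in a limited form. The branch rates planned for patients come from the people who determined the branches, and no stated step corrects them. They will tend to exaggerate the difference between the best and worst branches, by about 1.2 to 4 fold under assumed equal priors, cross-validated pruning and 10 to 20 binary candidates. In the moderate example the top branch is about 5 to 10 percentage points too high (23.5 − 18.8 = 4.7; 29.9 − 19.4 = 10.5). No single figure can be derived from the protocol.

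The chi-square comparison of the arms is not touched. This should be put right before the tool is released, but it does not threaten the trial's main conclusion.

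**What to change.** Add to the Specific Aim 2 paragraph of the Analytical Plan:
- The whole tree-building process, splitting and pruning together, is repeated inside an outer cross-validation or the bootstrap already planned, and the resulting optimism estimate is used to correct the branch rates.
- The correction is applied within treatment arm, for example: corrected rate = arm's overall rate + s·(branch rate − arm's overall rate), with s estimated in the outer loop. The pooled rate is not used as the target. The text should say how a branch that holds both arms is handled.
- The web and health-record tool shows only corrected rates, with bootstrap intervals that include the uncertainty in s.
- The prior or loss values and the pruning rule are named in advance, since they determine how large the bias is.

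This costs some code and wording and needs no new data. The drawbacks are that branches will look less different, and that with about 60 events the correction factor is itself imprecise, which is why its uncertainty belongs in the intervals.
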